#### 2.4.4. Control Group and Contamination

The delivery of intervention components will be under the control of the research team and will not be provided to the control-group services during the intervention period. The ECEC services in the control group will receive ‘usual care’. This includes the provision of a generic email with a link to the benefits of outdoor free play provided by a HPO [29]. 

### 2.5. Data Collection and Measures

Baseline data were collected in September–December 2022, while follow-up data collection will occur at approximately 6 months (primary timepoint, as it will occur approximately 2 years after COVID-19 guidelines) and 12 months post-baseline. The following data will be collected using either a telephone or online survey undertaken by a member of the research team. 

The nominated supervisor/service manager (or the opinion leader responsible for implementation of the SPSH program) will be asked to report on the feasibility and acceptability of the SPSH program, as well as the factors that influence the ongoing delivery of indoor–outdoor free-play programs in their service setting (Table 3). In addition, the Free Play Record (FPR) (a measure developed by the research team to assess service implementation of indoor–outdoor free-play programs and number of minutes of outdoor play) will primarily be completed by the most appropriate person or a person with knowledge of the performance of free play in the service (such as the opinion leader or nominated supervisor/service manager). 

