#### 2.2.3. Recruitment Procedures

All services in the sampling frame will receive an invitation email consisting of a recruitment package including an information statement and a link to an online consent form outlining study requirements and requesting participation. Once the consent form has been completed by the nominated supervisor, the online survey will automatically generate the recruitment survey to assess eligibility. A member of the research team will telephone services that have not responded after two weeks of receiving the email to discuss study details, confirm eligibility and request consent for study participation. Recruitment will continue until 20 ECEC services have consented [30,31]. Additionally, the research team will obtain the contact details of an educator who will assist with baseline data-collection processes. 

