### 2.3. Randomisation and Blinding

Following baseline data collection, services will be randomly allocated to either receive the SPSH program or usual care. A statistician will set up block randomisation using a computerised random number generator. Block randomisation will be used to ensure group allocation is approximately equal. This will be uploaded onto the online data-capturing platform (REDCap) [32,33], where service records are stored and concealed from statisticians. This pilot RCT will be conducted as an open trial as the sustainment strategy cannot be delivered without revealing the allocation to services. Therefore, services and data collectors will not be blinded to group allocation; however, those conducting data analysis will remain blinded to allocation for the main impact outcome (minutes of outdoor free play).

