#### 2.4.3. Intervention Components

Following baseline-data collection and randomisation, services allocated to the intervention group will receive the sustainment strategy. Specifically, services will be supported to continue to implement indoor–outdoor free-play programs.

The delivery of the SPSH program will include a minimum of four remotely delivered scheduled contacts, including two meetings via video calls and two support emails (see Table 2). The use of video calls has been found to be an effective and acceptable modality of delivering behaviour-change interventions for this type of setting as an alternative to face-to-face contact [56,57]. Contacts will target the nominated supervisor and an educator responsible for supporting the implementation of PA programs in the ECEC service. The intervention will be delivered by experienced health-promotion officers (HPO) employed by a local health-promotion unit with tertiary qualifications in physical activity, health promotion, nutrition and dietetics. They are employed by the local health services and have extensive experience supporting ECEC services in the delivery of healthy-eating and physical-activity programs. Additionally, the HPOs have undertaken behaviour-change training with an expert behavioural scientist to support behaviour change in this setting.

(a)Identify opinion leaders at the service:

ERIC Strategy: *Engage with local opinion leaders (i.e., supervisors or room leaders)*

Barriers Targeted: *Lack of administrative buy-in and support/leadership/management and lack of program leaders/facilitators/champions.*

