Develop a formal sustainment blueprint	*ERIC Strategy: Develop a formal implementation blueprint.* *Develop a formal blueprint which includes all goals and strategies to guide the implementation effort over time.* This is the introduction of an action plan (“Sustainability Action Plan”) for the service to implement best-practice sustainment strategies. This will track the implementation of the sustainment strategies and their progress.	Health promotion officer and Opinion leader	Introductory/3-month support meeting: Video call	Opinion leader	Provided: prior to introductory support call Discussed: during the introductory and 3-month support meeting Action: self-directed throughout the 6-month intervention period	Inner Contextual Factors *Organisational leadership/support*	Lack of centralised coordination ^a^ [39]	This aims to address these barriers by developing a Sustainability Action Plan, with defined strategies, to support the ongoing implementation of the EBP in the long term. The action plan is intended to be a self-directed tool that services use to track their progress in implementing the sustainment strategies, for which the opinion leader is responsible. This strategy allows more centralised leadership, led by the service, rather than externally.
						Processes ^b^ *Communications and strategic planning*	Absence of plan with defined measures ^a^ [45]	
Distribute educational materials	*ERIC Strategy: Distribute educational materials.* *Distribute educational materials (including guidelines, manuals, and toolkits) in person, by mail, and/or electronically.* A resource pack will be provided to services, which will include the following resources: Which external organisations support outdoor free play? How outdoor free play aligns with the National Quality Framework; COVID-19 outdoor-play guidance; Australian Physical Activity guidelines; Indoor–Outdoor Free Play in any Weather fact sheet; Benefits of Outdoor Free Play fact sheet; Shade and Heat fact sheet.	Health promotion officer	Email	Opinion leader	Provided: prior to introductory support meeting Discussed: during introductory support meeting	Outer Contextual Factors ^b^ *Funding environment and availability*	Lack of future external funding/financial support ^a^ [39,40,44,45,51,52]	The resource pack includes a fact sheet on a number of organisations that help ECEC services to deliver and encourage outdoor free play.

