Develop and implement tools for quality monitoring	*ERIC Strategy: Develop and implement tools for quality monitoring. Develop, test, and introduce into quality-monitoring systems the right input—the appropriate language, protocols, algorithms, standards, and measures (of processes, patient/consumer outcomes, and implementation outcomes) that are often specific to the innovation being implemented and sustained.* At the initial contact, an “ongoing monitoring plan” item will be added to the Sustainability Action Plan.	Health-promotion officer/Opinion leader	Email/Video call	Staff at the service	Provided: prior to introductory support meeting Discussed: during introductory support meeting and 3-month support meeting Action: self-directed throughout the 6-month intervention period	Processes ^b^ *Programme evaluation/data*	Accuracy in assessing impact of program ^a^ [45,51] Lack of clear data on effectiveness of program ^a^ [45]	The use of an ongoing monitoring tool, such as the FPR, will enable services to monitor their ongoing delivery of the EBP. This tool will highlight the gaps in indoor–outdoor free-play provision and address the lack of professional-development opportunities to upskill. In this way, staff will have the opportunity to self-monitor and adjust their practices. By using an ongoing monitoring tool, services will be able to accurately assess the impact of the program through child benefits, family feedback or other measures, thus enabling the identification of the effectiveness of indoor–outdoor free-play programs.
						**Processes** ^b^ *Communications and strategic planning*	Absence of plan with defined measures ^a^ [45]	

^a^ Barriers identified from interventions in schools [34]; ^b^ barriers identified from the NSW CATI (see intervention components); ^c^ barriers identified from interventions in ECEC settings [34].

**Table 2 ijerph-20-05043-t002:** Intervention schedule.

Month	Type of Contact	When	Method	Resources
0	Admin	Recruitment	Email	Recruitment pack
0	Admin	Recruitment	Call	Nominated-supervisor recruitment survey
0	Admin	Recruitment	Email	Free-play record
0	Admin	Recruitment	Email	Allocation email Opinion Leader position description
1	Admin	Baseline	Call	Administrative contact to book 1st intervention contact and identify Opinion Leader
1	First intervention contact	One-month timepoint Introductory meeting	Videoconference call	Introductory-meeting script Resource pack Sustainability action plan Guidance for addressing barriers

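### The Free Play Record may be completed by the opinion leader, a role assigned only in intervention services after randomisation, and nothing holds the reporter constant over time or between arms

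*Protocol article*

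**What the plan says.** Section 2.5 of the protocol article leaves the choice of FPR reporter to the service. It asks for a suitable person who knows how free play runs there, "such as the opinion leader or nominated supervisor/service manager". The same section describes that leader's stake when it lists who may answer the surveys: "or the opinion leader responsible for implementation of the SPSH program". Table 1 adds that the Sustainability Action Plan is a tool that services use "to track their progress in implementing the sustainment strategies, for which the opinion leader is responsible".

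The order of events is also stated. Section 2.3: "Following baseline data collection, services will be randomly allocated to either receive the SPSH program or usual care". Section 2.4.3: "Following baseline-data collection and randomisation, services allocated to the intervention group will receive the sustainment strategy". Identifying opinion leaders is strategy (a) of that package. Table 2 sends the position description with the allocation email at month 0 and lists, at month 1, "Administrative contact to book 1st intervention contact and identify Opinion Leader". For control services, Section 2.4.4 says that the intervention components "will not be provided to the control-group services during the intervention period".

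For baseline, Section 2.2.3 says that "the research team will obtain the contact details of an educator who will assist with baseline data-collection processes". Section 2.5.1, under sustainment, sends the FPR at baseline and follow-up to the supervisor or to educators, without fixing which. Section 2.3 leaves services and data collectors unblinded; only the analysts are blinded.

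**The concern.** Self-report in an open trial already carries some risk of favourable reporting in the intervention arm. What the plan adds is a reporter role that can differ by arm. By naming the opinion leader, it allows the outcome in an intervention service to be supplied by the person responsible for the program under test. No control service has anyone in that designated role, and neither arm had one at baseline.

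If reporters do change in this way, any difference in how the new person fills in the form appears as a difference between arms at 6 or 12 months and would be read as sustainment. The trial is a pilot and plans no confirmatory efficacy claim, but Section 2.6.7 lists potential sustainment among the data for the decision on a fully powered trial. The pilot is also meant to test the methods that the larger trial would inherit.

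**Working it through.** The protocol states no figure on this point that could be reproduced, so the check is to set the sections side by side and then write down the form of the bias.

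**1. Can the opinion leader report the outcome?** Yes. Section 2.5 names that person as an example.

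**2. Does the designated role exist in both arms?** No. It belongs to strategy (a) in Section 2.4.3, which goes to intervention services. Section 2.4.4 withholds the components from control services.

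**3. Does it exist at baseline?** No. Randomisation follows baseline (Section 2.3), and Table 2 identifies the leader at month 1.

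**4. Does any section hold the reporter constant?** No. Section 2.5.1 sends the FPR to the supervisor or educators at each time point. It does not ask for the same person at follow-up, and it does not exclude an opinion leader, who under strategy (a) may be the supervisor or another member of staff such as a room leader.

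**5. Is a switch plausible?** Yes, though it is not shown to happen. At months 6 and 12, Table 2 lists the FPR and the action plan for the same follow-up contact, and the opinion leader is responsible for the action plan. Table 1 also offers the FPR as an example of the service's own ongoing monitoring tool.

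**6. Would the planned analysis remove the effect?** Let f be the share of intervention services that switch to the opinion leader at follow-up. Let b be the average shift in recorded minutes compared with the reporter who would otherwise have completed the form. No control service can make this switch. Then, at follow-up:

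- mean recorded minutes, intervention = mean under the usual reporter + f × b
- mean recorded minutes, control = mean under the usual reporter
- bias in the between-arm difference ≈ f × b

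Section 2.6.2 adjusts for the baseline value of the outcome. Baseline was recorded before the role existed, so it carries no information on b, and the term f × b remains after adjustment.

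**7. How large is it?** The documents give neither f nor b. If no service switches, f = 0 and the bias is 0. For scale only: 20 services in two roughly equal arms is about 20 / 2 = 10 per arm, so each service that switches adds 1/10 to f and moves the estimated difference by about b / 10. A value for b would be a guess, so none is put in.

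**The case against.** The strongest reply is that a switch is only possible. The opinion leader is someone already on the staff who is given a role, not a new person. That person may be the nominated supervisor, or may have completed the baseline FPR, and then the reporter does not change. This stands, and it is why the point is about what the text permits.

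A reader might infer that an educator completed the baseline FPR everywhere, so that any opinion leader at follow-up is a new reporter. Section 2.2.3 says only that an educator helps with baseline data collection. It does not say who filled in the form.

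A reader might also try to size the bias from the FPR validation figure in Section 2.5.1: 7.6 × 5 = 38 minutes a week, against 84 × 5 = 420, or about 9%. The documents do not support this, for five reasons:

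- The 7.6 minutes is not stated to be per day.
- Its printed interval, −15 to 15, includes zero.
- It compares the FPR with direct observation, not one reporter with another.
- It concerns outdoor opportunity, whereas 84 minutes is the eligibility limit for indoor-only play.
- The 38 minutes would also need every intervention service to switch.

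It is also fair to say that the supervisor and an educator are themselves targets of the intervention contacts, so b is only the increment over reporters who are already unblinded and exposed. This stands too: fixing the reporter leaves the general problem of unblinded self-report in place.

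Finally, who fills in a form could be called operational detail that an article leaves to the full protocol. Silence alone would be no finding. Here, however, the article names a reporter whose designated role exists in one arm only.

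**Conclusion.** The point holds in a limited form. As written, the plan permits a change of reporter that is linked to arm and arises after baseline, in an unblinded self-reported outcome, and adjustment for baseline does not remove it. The size is unknown: about f × b, from zero upward. That a switch would favour the intervention is an inference from the opinion leader's responsibility for SPSH; no data in the documents show it.

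The conclusion rests on two readings: that the opinion leader is designated only in intervention services, which Sections 2.4.3 and 2.4.4 and Table 2 support, and that no rule keeps the reporter constant, since none is stated. It does not rest on any assumed number of minutes. It does not show that the pilot's estimate is biased, only that an avoidable route to differential reporting is open. The change is worth making because it is cheap and follow-up is still to come.

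**What to change.** Baseline was collected in September–December 2022 and the trial is in the delivery stage, so the change has to work from whoever actually reported at baseline. Imposing one fixed role now, such as the educator named at recruitment, could itself cause a switch in services where someone else completed the baseline form.

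- State that, in both arms, the person who completed the service's baseline FPR completes the 6- and 12-month FPRs where possible.
- Set one fallback rule common to both arms, for example the nominated supervisor.
- Remove the opinion leader as a named FPR reporter in Section 2.5, except where that person was the baseline reporter.
- Record the reporter's role on each FPR and tabulate it by arm and time point, so that the share of services with a changed reporter can be seen.

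The cost is one instruction to services and one data field. The downside is that where the baseline reporter has left, the fallback may know the daily routine less well.

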#### 2.5.1. Outcomes

*(i)* *Acceptability, feasibility, and potential impact of the SPSH program on the sustainment of indoor–outdoor free-play program (defined as ongoing implementation of the EBP) in ECEC services*;

*(1) Acceptability of the SPSH program:*

This is defined as ECEC service-staff perceptions of the extent to which the SPSH program is agreeable, palatable, or satisfactory [73].

During the 6-month post-baseline follow-up telephone or online survey, the service manager at the intervention services will be asked to report on 8 items capturing information related to the acceptability (e.g., attitude towards the SPSH program, burden, ethicality of the program, coherence, effectiveness, self-efficacy) of the SPSH program. These items are underpinned by the Theoretical Framework of Acceptability (TFA), a validated framework used to assess the acceptability of healthcare interventions from the perspectives of intervention deliverers and recipients [74].

This survey consists of 7 items measured on a Likert scale with response options ranging from 1 to 5. The domains include their affective attitude towards SPSH (“Did you like or dislike SPSH?”), the effort involved, or “Burden” (“How much effort to engage in SPSH?”), the perceived effectiveness of SPSH (“SPSH has helped to continue the sustainment of indoor–outdoor free-play programs?”), intervention coherence (“is it clear how SPSH has helped to continue the sustainment of indoor-outdoor free play programs”), self-efficacy (“How confident did you feel about participating in SPSH?”), opportunity costs (“Participating in SPSH interfered with other priorities”) and general acceptability (“How acceptable was SPSH?”). Generally, 1 is a negative response/disagreement with the statement, while 5 is a positive response/agreement with the statement, except for Burden (domain 2) and Opportunity costs (domain 6), where 1 is a positive response, while 5 is a negative response. The 8th item is an open-ended question to capture any further comments on the acceptability of the SPSH program. 

*(2) Feasibility of the SPSH program:*

This is defined as ECEC services’ perceptions of the extent to which the SPSH program can be successfully used or carried out at scale within different organisations or settings [73].

Data on the number of minutes that children are provided with indoor-only, indoor–outdoor, and outdoor-only free play from a randomly selected week will be collected via the FPR. The FPR is adapted from existing ECEC measures of outdoor play: Environment and Policy Assessment and Observation—Self-Report (EPAO—SR) and Nutritional and Physical Activity Self-Assessment for Child Care (NAPSACC) [77,78]. The adapted FPR measure has been pilot-tested with ECEC services and has been reported to take less than 5 min/day on average and to be acceptable and easy to complete. Further, our unpublished data indicate that the Free Play Record overestimates opportunities for outdoor free play (the primary outcome) by just 7.6 min (95% CI −15, 15) compared to direct observations (*p* < 0.3651). The FPR will be provided to the nominated supervisor/service manager or educators at each ECEC service electronically, via email, by the research team, at baseline and during the follow-up period. The educators/nominated supervisor(s) will be asked to complete the FPR for each session of free play throughout the day across the selected week (5 consecutive days) and return the completed FPR to the research team. If not returned, a follow-up email or phone call will then be made to the appropriate delegate to follow up on the progress of FPR completion. When the research team receive the completed FPR, a phone call will be made to the ECEC service to obtain any missing data, clarify non-legible responses, if required and assess any specific challenges to completing the FPR. The research team have successfully undertaken this with 90 services as part of previous trials [79].

*(4) Adoption of SPSH-program recommendations:*

Adoption is defined as the intention, initial decision, or action undertaken to employ an innovation or evidence-based practice [80]. This will be assessed according to how many strategies within the “Sustainability Action Plan” are completed by the 6-month time point, to determine how many sustainment strategies were applied according to the intentions of the SPSH program. 

*(ii)* 
*Feasibility of use of trial methods to inform the conduct of a fully powered RCT*

*(1) Feasibility of the trial methods:*

In order to inform a fully powered RCT and to assess whether the trial methods are feasible and replicable, project records will be used to report consent rate, percentage of missing data from completion of the FPR (internal self-reported measure), comparison of consenter/non-consenter characteristics, attrition rate, withdrawal and reasons and contamination [26,27]. 

*(2) Fidelity to delivering the SPSH program:*

Fidelity is defined as the degree to which the SPSH program was implemented as described or intended in the original protocol [80]. Fidelity will be assessed using project records, which will determine the extent to which each sustainment strategy was delivered by the HPO. This will be undertaken by the research team documenting these data during recruitment and intervention delivery on a spreadsheet. 

*(iii)* 
*Barriers to and facilitators of the sustainment of indoor–outdoor free-play programs in ECEC services*

*(1) Barriers to and facilitators of indoor–outdoor free play:*

During the baseline and 6-month follow-up telephone/online surveys with the nominated supervisor/service manager, barriers, and facilitators to sustaining the EBP will be assessed. This will be conducted using an adapted measure of the 29-item scale, which measures sustainability determinants across the constructs of the Integrated Sustainability Framework (outer and inner contextual factors, processes, and characteristics of the intervention) developed by the team. This adapted 9-item scale measures the outer contextual factors and processes that are perceived to be influential in intervention sustainment in ECEC settings. The nominated supervisor/service manager will be asked to rate their level of agreement with a number of items on a scale from 1 (completely disagree) to 5 (completely agree). 

*(2) ECEC service characteristics*

Data regarding ECEC service characteristics, including service type, age group of children at the service, operating hours, number of children enrolled aged three to six years and number of educators at the service, will be collected via a baseline survey of ECEC nominated supervisors/service managers and educators. Service locations’ postcodes will be used to determine socioeconomic status (SES) and rurality. Services with postcodes ranked in the top 50% of state postcodes based on the 2016 Socio-Economic Indexes for Areas (SEIFA) [81] will be classed as “higher socioeconomic areas”, whereas those in the lower 50% will be classed as “lower socioeconomic areas”. 

*(3) Cost*

Similar to a previous analysis [82], the direct cost of each sustainment strategy delivered by the HPOs, including labor (i.e., HPO preparation, administration and delivery of the program) will be calculated. Service-delivery costs will be recorded by the HPOs delivering the interventions. Costs in AUD, 2022/2023 will be calculated by multiplying the time spent (in hours) on each sustainment strategy by the hourly wage rate of HPOs delivering the intervention. The cost for nominated supervisor/educators to receive the SPSH program delivered by the HPOs and time taken to implement the strategies will also be calculated. Similar to previous studies examining the cost of receiving interventions within ECEC settings [83], costs will be calculated and multiplied by the time spent (in hours) receiving the SPSH program by the estimated hourly wage rate of the nominated supervisors/service managers and Educators [84]. The time spent will account for the services representatives’ attendance at all meetings and implementation of the strategies in their respective service settings. 

